##### Per-protocol population

The per-protocol population will include patients who would consume more than 80% of the prescribed doses of the study drug and complete the trial.

Effectiveness will be evaluated by ITT principle and per-protocol principle. When analysis results are different, the ITT principle will be considered for the main analysis and subordinately, we will compare the results of the analysis based on the per-protocol principle. Demographic and safety test will be analyzed by ITT principle and the data for safety test will be used without adjustment.

#### Primary endpoint

An independent t-test (or Mann-Whitney U test) will be used to compare the mean percentage change in total lesion counts from baseline to the end of the treatment between the two groups in terms of the primary outcome. Superiority will be confirmed when there are statistically significant differences. The level of significance will be set at a *P* value of 0.1.

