### Hypothesis

The primary objective is to investigate whether herbal medicine treatment for dysmenorrhea can reduce the number of acne vulgaris lesions in comparison with that reported with placebo treatment. The primary null hypothesis is as follows: Eight-week GBH and DJS treatment does result in any change in the number of acne vulgaris lesions between the treatment group and placebo group.

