### Sample size calculation

We referred to similar studies that investigated the effects of herbal medicine for dysmenorrhea [17, 21]. The mean difference for the treatment group and placebo group was assumed to be 2.21 and 1.28, respectively. Pooled SD was assumed to be 2.24 based on the same studies. We set α at 0.05 and 1-β at 0.8 and calculated the necessary sample size. Assuming a 15% dropout rate and an allocation ratio of 1, the sample size was calculated to be 116 (58 participants in each group).

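### The primary test uses a significance level of 0.1 although the trial was sized at 0.05, with no sidedness or reason given; if both levels are two-sided, the type I error is 10% rather than 5%

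*Protocol article*

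**What the plan says.** Under *Sample size calculation* the protocol article states: "We set α at 0.05 and 1-β at 0.8 and calculated the necessary sample size". The inputs given there are "The mean difference for the treatment group and placebo group was assumed to be 2.21 and 1.28, respectively" and "Pooled SD was assumed to be 2.24 based on the same studies". With 15% dropout and 1:1 allocation the result is 116 participants, 58 per group.

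Under *Statistical analysis – Primary endpoint* the test is specified as follows: "An independent t-test (or Mann-Whitney U test) will be used to compare the mean percentage change in total lesion counts". The decision rule is "Superiority will be confirmed when there are statistically significant differences", and the threshold is "The level of significance will be set at a *P* value of 0.1".

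The article does not say whether either level is one- or two-sided. The only indirect evidence is the null hypothesis under *Hypothesis*, which concerns "any change in the number of acne vulgaris lesions between the treatment group and placebo group" and names no direction. The opening paragraph of *Statistical analysis* rules out an interim analysis.

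**The concern.** The level at which a trial is sized and the level at which its primary hypothesis is tested should be the same quantity. Here they differ by a factor of two, and the looser one governs the claim of superiority. None of the usual explanations is offered: alpha is not split across interim looks, the trial is not labelled exploratory, and no one-sided/two-sided convention is stated.

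The stake is the strength of evidence behind the trial's main conclusion. With, say, P = 0.07, the written rule confirms superiority, although the trial was designed around 0.05. With both figures on record, the choice of threshold could also be argued over once the result is known, which pre-specification is meant to prevent.

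**Working it through.** **1. Type I error of the written rule**

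Inputs: 0.1 (*Primary endpoint*) and 0.05 (*Sample size calculation*). Assumption: both are two-sided. With a symmetric two-sided test, half of the error falls in each direction.

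| Level | Total type I error | False claim for herbal arm |
|---|---|---|
| 0.05 | 5% | 0.05/2 = 2.5% |
| 0.10 | 10% | 0.10/2 = 5% |

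A simulation of the t-test under the null with 58 per group (200,000 trials) gave 5.0% and 9.9% in total, and 2.5% and 5.0% in one direction.

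**2. Does the stated sample size show which level was meant?**

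Formula per group: n = 2 × [SD × (z for alpha + z for power) / difference]², then divide by 0.85 for 15% dropout. SD = 2.24 and power = 0.80 throughout.

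*Literal difference, 2.21 − 1.28 = 0.93:*
- Two-sided 0.05: n = 91.07, so 92; 92/0.85 = 108.2, so 109 per group, 218 in total.
- Two-sided 0.10 (the same as one-sided 0.05): n = 71.73, so 72; 72/0.85 = 84.7, so 85 per group, 170 in total.
- One-sided 0.10: n = 52.30, so 53; 53/0.85 = 62.4, so 63 per group, 126 in total.

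None of these gives 116.

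*If 1.28 was itself the intended difference (an inference, not stated):*
- Two-sided 0.05: n = 2 × [2.24 × (1.960 + 0.842)/1.28]² = 48.07, so 49; 49/0.85 = 57.6, so 58 per group, 116 in total. This is the stated figure.
- Two-sided 0.10: n = 37.87, so 38; 38/0.85 = 44.7, so 45 per group, 90 in total.

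Of these two-group readings, the one that returns 116 uses two-sided 0.05; none at two-sided 0.10 or one-sided 0.05 does. This is supporting evidence only, because it requires reading 1.28 as something other than the placebo value the article says it is.

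**3. What the stricter level costs in power**

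Two-sample t-test (noncentral t), 49 evaluable per group (58 × 0.85 = 49.3):

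| Difference | Difference/SD | Two-sided 0.05 | Two-sided 0.10 |
|---|---|---|---|
| 0.93 (literal) | 0.415 | 53% | 65% |
| 1.28 (inferred) | 0.571 | 80% | 88% |

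These figures use the article's own sizing inputs, which come from dysmenorrhea studies. They show the relative cost of the threshold, not the actual power for percentage change in lesion count.

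**The case against.** **Sidedness.** The best defence is that 0.05 in the sizing is one-sided and 0.1 in the test is two-sided. Both then give a 5% chance of falsely favouring the herbal arm, and nothing is doubled. The article does not exclude this, so the doubling must stay conditional. But the article does not say it either, the non-directional null hypothesis points the other way, and the sample size does not support it (170 or 90 in total, not 116).

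**Exploratory purpose.** The *Discussion* looks ahead to a larger trial based on this one, and a justified, labelled 0.10 could be coherent in an early study. That stands as a possibility. However, the article neither calls the trial exploratory nor gives this as the reason for 0.1, and it speaks of confirming superiority.

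**Stronger readings that do not hold.** Three are tempting.
- A reader might infer that a significant advantage for placebo would count as confirming superiority, since the rule names no direction. The objective under *Hypothesis* asks whether treatment reduces lesions relative to placebo, so the intended direction is clear enough. The wording is loose, but the rule is not defective on that account.
- A reader might say that P between 0.05 and 0.1 is positive in one section and negative in the other. The sample size section contains a design input, not a decision rule. The only rule for the primary endpoint is the one at 0.1.
- A reader might argue that 0.1 is unnecessary because 49 per group already gives 80% power at 0.05. That is true only if 1.28 was the difference. On the literal 0.93, neither level reaches 80%.

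**Conclusion.** The plan is wrong as written: it sizes the trial at 0.05 and confirms superiority at 0.1, without sidedness, reason or reconciliation. This contradiction rests on no assumption.

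Its size does. If both levels are two-sided, total type I error is 10% against 5%, and the chance of a false claim of herbal benefit is 5% against 2.5%. Two-sided is the more plausible reading, but it is not stated. The practical effect is confined to P values between 0.05 and 0.1, which would be declared superiority at a level looser than the design alpha.

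That 116 does not follow from the literal difference is a separate problem. Low power on those inputs is a reason to revisit the sample size, not to relax the threshold.

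**What to change.** Use one alpha and state its sidedness in both *Sample size calculation* and *Primary endpoint*. Two-sided 0.05 is the natural choice, since it keeps the design alpha already stated. The primary endpoint section could then read: *The primary test is two-sided at the 0.05 level; superiority is concluded if P < 0.05 and the difference favours the herbal group.* The direction clause only makes explicit what the objective already implies.

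If the sponsor does want 0.10, the article should say why, state the sidedness, use the same level in the sizing, and describe the strength of the claim accordingly.

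The edit is a change of wording and should be made before unblinding. Its real cost is the loss of power shown above: about 12 percentage points on the literal difference (65% to 53%) or 8 if 1.28 was intended (88% to 80%).

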#### Secondary endpoint

An independent t-test (or Mann-Whitney U test) will be used for continuous variables and Chi-square test (or Fisher’s exact test) for categorical variables between groups. Group effect, time effect, and group × time effect for repeat measurement data will be analyzed by repeated-measures analysis of variance (ANOVA) or repeated-measures analysis of covariance (ANCOVA).

## Discussion

Nowadays, adult acne, especially female adult acne is increasing considerably [6].Acne is primarily associated with phychosocial impairment. It can affect an individual’s self-esteem and may cause anxiety, withdrawal, decreased ability to focus on work, depression, and interpersonal conflicts, thereby impairing overall quality of life [22–25].

Acne related to menstrual cycle is often nonresponsive to conventional therapies; thus, hormonal therapy, such as oral contraceptives, is used [15]. However, oral contraceptives have adverse effects including nausea/vomiting, breast tenderness, headache, spotting/breakthrough bleeding, edema of the lower extremities in the venous system, and with some, weight gain [15]. Due to limited treatment options, acne related to menstrual cycle is considered a challenging clinical problem. Despite clinical evidence that acne associated with menstruation abnormalities naturally improves when menstruation recovers to normal, there have only been few studies on the effects of dysmenorrhea treatment on acne vulgaris at childbearing age. This is the first protocol to investigate the efficacy of herbal medicines prescribed in dysmenorrhoea treatment on the accompanying acne. This study is a randomized, placebo-controlled, double-blind, parallel-group multicenter trial. We designed this clinical trial in accordance with the Consolidated Standards of Reporting Trials guidelines [26]. The validated evaluation tool will be used to assess the severity of acne and dysmenorrhea. Moreover, pattern identification will be used to reflect clinical field. We believe that this research will provide important evidence regarding the use of herbal medicines in the treatment of acne along with menstrual abnormalities. Moreover, a larger scale clinical trial evaluating the efficacy and safety of GBH and DJS in treating menstruation-related acne, based on this study and specific Korean patterns identified, will be possible in future.

## Abbreviations

AE: Adverse event
ALT: Alanine aminotransferase
ANCOVA: Analysis of covariance
ANOVA: Analysis of variance ANOVA
AST: Aspartate aminotransferase
BMI: Body Mass Index
BUN: Blood urea nitrogen
DJS: Dangguijagyag-san
GBH: Gyejibokryung-hwan
hCG: Human chorionic gonadotropin
ITT: Intent-to-treat
NRS: Numeric rating scale
NSAID: Nonsteroidal anti-inflammatory drug
SAE: Serious adverse event
TKM: Traditional Korean medicine
VMSS: Verbal multidimensional scoring system
